#### Concomitant care

In both the usual care and intervention arms, participants will be permitted to continue any treatment they were engaged with at entry to the trial. Concomitant care will be assessed via self-report questionnaire and routinely collected Government data (see below).

#### Treatment adherence

In the intervention arm, adherence to treatment in the minimal/mild and moderate depressive severity groups will be assessed using website analytics within myCompass and This Way Up (i.e. tracking individual log-ins, access of components, completion of modules and lessons). In the severe group, adherence to the treatment plan will be assessed by the Target-D CM as part of the planned follow-up schedule.

In the control arm, in order to compare “usual care” before and during participation in the trial, information about health service use will be collected at each study assessment (see below).

### Outcomes

Outcome measures will be collected at baseline and three and 12 months post randomization. These time points were selected to balance the benefits of multiple assessments against the risk of unduly burdening participants. They allow us to examine both the immediate and longer-term effect of the intervention and, because they are commonly used in trials of mental-health interventions, will permit comparisons to be drawn with other relevant studies.

#### Primary outcome

The primary outcome is the difference between the two treatment arms in mean depressive symptom severity at three months, controlling for baseline depressive symptom severity. Depressive symptom severity was selected as the outcome measure rather than a clinical diagnosis of major depressive disorder as it is more relevant to the design and delivery of stepped mental healthcare.

#### Secondary outcomes

Secondary outcomes include difference between study arms in mean depressive symptom severity at 12 months and mean mental-health self-efficacy and anxiety at three and 12 months. The cost-effectiveness of the intervention over the study period will comprise an additional secondary outcome.

### Sample size

Sample size calculation was based upon our trial experience, a systematic review of depression trials [55] and current data from the *diamond* study [39]. The primary objective is to test for a standardized effect size of 0.2SD in mean depressive symptoms at three months between the intervention and comparison arms. However, we based our calculations on our planned subgroup analyses because the sample size required would need to be larger to test for difference between study arms within each of the three depressive symptom severity groups than combined. Therefore, we based sample size on detecting a standardized mean difference of 0.2 between arms for the minimal/mild group (given the potential floor effect we anticipate a smaller intervention effect). We hypothesized a standardized effect size of 0.5 in the moderate and severe depressive symptom severity groups as they have room for greater improvement and will receive more intensive treatments.

Based on the CPT development work, we anticipated that 70% of participants will be classified as being likely to have minimal/mild depressive symptoms, 15% as moderate, and 15% as severe depressive symptoms at three months. We used these estimates to extrapolate the total sample size needed to ensure that we had sufficient power for the sub-group analyses. Based on these assumptions, we required 158 (78 in each arm) participants in each of the moderate and severe groups to detect a standardized effect size of 0.5 and 740 (370 in each arm) in the mild/minimal group to detect a smaller standardized effect size of 0.2, with 80% power and 5% significance level for a two-sided test.

This leads to an anticipated sample size of 1056 participants (528 in each arm), which is also sufficient for the primary objective to detect a standardized effect size of 0.2 in the mean PHQ-9 between study arms, with 90% power and 5% significance level. A standardized effect size of 0.2 is equivalent to a mean change of 1.35 points in the mean depressive symptoms assuming a standard deviation on 6.75 (based on *diamond* data). This effect size is in keeping with those found in systematic reviews of interventions to decrease depressive symptom severity in primary care [57].

We inflated the required sample size to 1320 to allow for 20% attrition at 12 months. Based upon documented response rates and depressive symptom prevalence gathered from our experience of recruiting participants with depressive symptoms in the primary care setting [39], achieving this sample size at baseline requires that we invite 22,000 adults to complete the screening tool (Fig. 1).

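### The stated subgroup sizes are not the 80%-power requirements: 370 per arm gives about 78% at 0.2 SD in the minimal/mild group, 79 per arm gives about 88% at 0.5 SD, and 78 should read 79

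*Protocol article*

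**What the plan says.** All the relevant figures are in the Sample size section of the protocol article. The effect sizes are set by group: "we based sample size on detecting a standardized mean difference of 0.2 between arms for the minimal/mild group", and "We hypothesized a standardized effect size of 0.5 in the moderate and severe depressive symptom severity groups". The sizes follow: "we required 158 (78 in each arm) participants in each of the moderate and severe groups", and "740 (370 in each arm) in the mild/minimal group to detect a smaller standardized effect size of 0.2, with 80% power". Both are tied to one error specification: "with 80% power and 5% significance level for a two-sided test". The total is then given: "This leads to an anticipated sample size of 1056 participants (528 in each arm"). It is said to suffice also for 0.2 SD overall with 90% power, and it is inflated to 1320 for 20% attrition at 12 months.

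The same section says that the calculation was based on the subgroup analyses because they need more participants than the overall comparison, and that expected shares of 70%, 15% and 15% were used to arrive at the total. The Recruitment section (primary care patients) says that recruitment goes on until the number in each severity group has been reached.

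**The concern.** The section gives every input needed to check the group sizes: effect size, power, significance level, sidedness and 1:1 allocation. A standard two-sample calculation from these inputs gives neither 370 nor 78. The discrepancies run in opposite directions (370 is too few, 78 too many), so neither rounding nor a single omitted factor explains both. The arm figures also disagree with the totals beside them, since twice 78 is not 158.

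At stake is the accuracy of the declared basis for the sample size. The within-group comparisons are the second of the secondary objectives, and the group numbers govern when recruitment stops. A reader who relies on the text would credit the minimal/mild comparison with slightly more power than it has, and would take 158 for a calculated requirement.

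**Working it through.** **Inputs** (Sample size section; the 1:1 allocation is from Trial design): two-sided alpha 0.05, so z = 1.960; subgroup power 80%, so z = 0.8416; overall power 90%, so z = 1.2816; effects 0.2 SD (minimal/mild and overall) and 0.5 SD (moderate, severe); SD 6.75 PHQ-9 points; shares 70/15/15. No baseline-outcome correlation is stated, so the first calculation is unadjusted.

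**Formulas** (normal approximation): n per arm = 2(z_alpha + z_power)² / d², and power = Φ(d·√(n/2) − 1.960). Noncentral t results are given alongside.

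**1. What reproduces.**
- Overall, 528 per arm, d = 0.2: 0.2 × √264 = 3.250; 3.250 − 1.960 = 1.290; power 90.1% (t: 90.1%).
- Inflation: 1056 / 0.80 = 1320.
- Group totals: 740 + 158 + 158 = 1056.
- Effect in points: 0.2 × 6.75 = 1.35.

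**2. Minimal/mild, d = 0.2.**
- Required for 80%: 2 × (2.8016)² / 0.04 = 392.4, so 393 per arm (t: 394), or 786 to 788 in total against the stated 740.
- Power at 370 per arm: 0.2 × √185 = 2.720; 2.720 − 1.960 = 0.760; power 77.6% (t: 77.5%).
- Effect detectable with 80% power at 370 per arm: 2.8016 / √185 = 0.206 SD, or 0.206 × 6.75 = 1.39 points against 1.35.

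**3. Moderate and severe, d = 0.5.**
- Required for 80%: 2 × (2.8016)² / 0.25 = 62.8, so 63 per arm (t: 64), or 126 to 128 in total against the stated 158.
- Power at 78 per arm: 0.5 × √39 = 3.122; 3.122 − 1.960 = 1.162; power 87.7% (t: 87.3%).
- Power at 79 per arm: 0.5 × √39.5 = 3.142; 3.142 − 1.960 = 1.182; power 88.1% (t: 87.8%).

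**4. Sums by arm.** 2 × 78 = 156, not 158; 370 + 78 + 78 = 526, not 528. With 79: 2 × 79 = 158 and 370 + 79 + 79 = 528. This is one slip seen in two places.

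**5. Could another specification give both numbers?**
- One-sided 5%: 310 and 50 per arm.
- Baseline adjustment, multiplying n by (1 − r²), with r = 0.25: 392.4 × 0.9375 = 367.9, so 368 for 0.2 SD; 62.8 × 0.9375 = 58.9, so 59 for 0.5 SD.
- Alpha 0.025: 77 for 0.5 SD, but the text states 5%.

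None of these gives 370 together with 78 or 79.

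**6. Relation to the shares.** 0.70 × 1056 = 739.2 and 0.15 × 1056 = 158.4. In the other direction, 740 / 0.70 = 1057 and 0.15 × 1057 = 158.6. The group totals are consistent with the shares either way.

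**7. Attrition.** 70% of 1320 is 924, or 462 per arm. At 20% loss, 462 × 0.80 = 369.6 per arm, back to about 77.5%. At 10% loss, 415.8 per arm remain, giving about 82%. The 394 per arm needed for 80% are kept if loss is below 1 − 394/462 = 14.7%.

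**The case against.** The strongest counter-argument is that the planned analysis is adjusted. The Outcomes section defines the primary outcome as controlling for baseline severity, and Statistical methods carries baseline adjustment into the models, with similar models within each severity group. Taking the baseline-outcome correlation r as an assumption, 370 per arm gives about 80% at r = 0.25, 84% at r = 0.4 and 88% at r = 0.5. Some positive correlation is expected, because the prediction tool itself uses baseline PHQ-9 items. This stands as a reason to expect the real shortfall to be small or absent. It does not make the stated figures right: the calculation mentions no correlation, the value within a severity group is unknown, and r = 0.25 moves the 0.5 SD requirement further from 158.

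It is also fair to say that the 20% attrition is a 12-month allowance while the primary time point is three months, so more than 370 per arm may be available then. That depends on three-month loss staying below about 15%, which the article does not state.

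Two stronger readings are tempting. A reader might infer that all the subgroups miss 80% power; the moderate and severe groups in fact exceed it. A reader might also infer that 1056 was sized for the overall test and then split downwards, contrary to the stated rationale. The document does not settle this. The overall test needs 526 to 527 per arm (1052 to 1054), which is close to 1056 but not equal to it, and 740 / 0.70 = 1057 fits at least as well and matches the described step of extrapolating a total from the shares. On that route 158 is a by-product of the shares, and only the word required is inaccurate.

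**Conclusion.** The point holds as a correction of stated figures. On the section's own inputs, without baseline adjustment, the minimal/mild group has about 78% power at 0.2 SD, roughly 2.5 percentage points under the stated 80%. In terms of detectable effect the gap is 0.206 against 0.200 SD, or about 0.04 PHQ-9 points. The moderate and severe groups have about 88% at 0.5 SD, so their stated power is understated and 158 is not an 80% requirement. The figure of 78 per arm is a slip for 79.

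The consequence is limited. The only shortfall is in one comparison belonging to a secondary objective, and the overall primary comparison has its stated 90%. The result assumes equal arms, a two-sample comparison of means and no variance reduction from covariates. A within-group correlation of about 0.25 or more would remove the minimal/mild shortfall but would leave the 158 and 78 figures wrong as described.

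**What to change.** Amend the Sample size text and leave enrolment unchanged:

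- **Minimal/mild:** state that 740 (370 per arm) gives about 78% power for 0.2 SD, or 80% for 0.206 SD. Alternatively, keep 80% and state the baseline-outcome correlation relied on (about 0.25 would do) and its source.
- **Moderate and severe:** state that 158 (79 per arm) gives about 88% power for 0.5 SD, and describe 158 as following from the expected 15% share, not as the number needed for 80%.
- **Per-arm figure:** change 78 to 79, so that the arms sum to 528.
- **Leave as they are:** 90% power overall at 528 per arm, and the inflation to 1320.

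The cost is a text correction, with one stated power becoming slightly less favourable. No analysis, group target or recruitment total changes. For scale, raising only the minimal/mild group to 786 would mean 786 + 158 + 158 = 1102 completers and 1102 / 0.80 = about 1378 recruited, which a gap of this size on a secondary objective does not call for.

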**Fig. 1 Fig1:**
[figure not shown]
Expected progression of participants through the study

### Recruitment

#### Study sites

We will follow principles of good recruitment by engaging with all stakeholders, branding the Target-D trial, and using a well-developed engagement strategy [58]. We will recruit general practices via our Victorian Primary Care Practice-Based Research Network (VicReN), which has around 200 GP members located in Victoria, Australia. Practices will be contacted by phone and/or email to introduce the study and establish interest. One of the Target-D researchers will then visit interested practices to determine eligibility, provide detailed information about the study, and gain consent to participate. This process will continue until sufficient practices are recruited to obtain the required sample size.

To enhance GP and practice staff engagement in the trial and the activities necessary to make it function, we will be guided by the principles of Normalization Process Theory (NPT) [59]; namely, coherence (meaning of the trial to GPs and staff), cognitive participation (commitment and engagement), collective action (the work GPs and staff do to make the trial function), and reflexive monitoring (GP and staff appraisal of the trial). In each participating practice, GPs and staff will be given a training session clarifying the goals and activities of the trial, in order to instill a sense that the trial is a good idea and worth committing to. In addition, we will clearly outline the trial procedures and how they are likely to affect the work of the practice, with emphasis on how the trial fits with the overall goals of the general practice.

#### Minimizing contamination

Randomizing individuals that were recruited from the same general practice, where the clinician is not blinded to the participant’s study arm or the intervention is implemented at the practice level, may have a greater risk of contamination between intervention and comparison arms than randomizing a group of individuals that do not belong to the same practice [60]. However, the risk of contamination in this trial is expected to be minimal because of several factors. First, recruitment of participants will be conducted in the waiting room by an RA who is not involved in delivering the study intervention and has no access to the allocation schedule. While patients in the waiting room or from the same family or friendship groups may share information, it is unlikely that this will impact the intervention effect as the intervention can only be accessed by permission of the study team. Second, GPs will only be informed of participants allocated to collaborative care treatment. Even if other patients inform their GP that they are participating in Target-D, GPs will not be informed of their treatment allocation nor be able to access study interventions for UC+ patients. Third, the intervention for minimal/mild groups will be via Internet-based programs delivered outside the practice, reducing the potential for practice-based contamination. We will assess the number of UC+ participants registering for these programs to measure the degree of potential contamination. Fourth, the risk that GPs may implement some of the intervention to patients predicted to have severe symptoms and allocated to the UC+ group is small. We anticipate that fewer than ten such participants will be recruited per practice and this small number of patients will be seen by different GPs. We have successfully used a similar approach in a previous RCT in general practice; data from this trial showed very low levels of interaction between comparison participants and the GP during the study time-frame [61].

#### Primary care patients

Potential participants will be alerted to the study via posters and information pamphlets displayed in practice waiting rooms; an awareness raising strategy used by the research team previously. All study materials and procedures were developed and tested with focus groups and individual feedback to ensure they are engaging and user-friendly. Upon completion of the screening survey, eligible participants will enter their name, telephone number, and email address into an online form. They will then be presented with an electronic copy of the plain language statement and provide online consent to participate.

To achieve our required sample size, trained RAs will approach an average of 50 adults per practice per day, taking approximately 440 working days to approach our required 22,000 adults. These numbers are typical of RCTs in primary care and we have achieved similar numbers in previous successful studies [39, 62, 63]. While this number may seem ambitious, several factors contribute to it being achievable. First, we have designed the trial so that participants are recruited by RAs rather than expecting already time-pressured GPs and practice staff to take responsibility for recruitment. Second, the 22,000 patients RAs will approach include all adult patients in the waiting room; RAs or practice staff are not required to identify only those patients who are presenting to the GP for mental health reasons. Finally, we have tried this approach out in a clinic and shown that on weekdays alone an RA can approach at least 50 patients per day and invite 1100 patients per month to the study. Our pilot work has shown that an RA spends only 1 or 2 min with each patient and can comfortably approach 150 patients in a working day. Based on this experience and after accounting for weekend recruitment in some practices, we anticipate participant recruitment to take place over approximately 18 months. Recruitment of participants will continue until the numbers within each depressive symptom severity group have been met.

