**Methods:**

The Target-D study is an individually randomized controlled trial. Participants will be 1320 general practice patients with depressive symptoms who will be approached in the practice waiting room by a research assistant and invited to complete eligibility screening on an iPad. Eligible patients will provide informed consent and complete the CPT on a purpose-built website. A computer-generated allocation sequence stratified by practice and depressive symptom severity group, will randomly assign participants to intervention (treatment recommendation matched to predicted depressive symptom severity group) or comparison (usual care plus Target-D attention control) arms. Follow-up assessments will be completed online at three and 12 months. The primary outcome is depressive symptom severity at three months. Secondary outcomes include anxiety, mental health self-efficacy, quality of life, and cost-effectiveness. Intention-to-treat analyses will test for differences in outcome means between study arms overall and by depressive symptom severity group.

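### The rule to recruit until each severity group is filled is not reconciled with the planned 1320, and the group numbers are not the 80%-power sizes they are said to be

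*Protocol article*

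**What the plan says.** The abstract gives a single planned total: "Participants will be 1320 general practice patients with depressive symptoms". Under Sample size, the protocol chooses to size the trial on the three severity subgroups. For the two smaller groups the stated requirement is "158 (78 in each arm) participants in each of the moderate and severe groups to detect a standardized effect size of 0.5". For the largest group the corresponding figure is "740 (370 in each arm) in the mild/minimal group to detect a smaller standardized effect size of 0.2". The error rates that the section attaches to all of these are the same: "with 80% power and 5% significance level for a two-sided test". The expected mix is that "we anticipated that 70% of participants will be classified as being likely to have minimal/mild depressive symptoms, 15% as moderate, and 15% as severe". The group numbers sum to 1056, and then "We inflated the required sample size to 1320 to allow for 20% attrition at 12 months". The 22,000 invitations are derived from 1320, and the Primary care patients subsection of Recruitment turns them into about 440 working days and roughly 18 months.

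That subsection then closes with the operative rule: "Recruitment of participants will continue until the numbers within each depressive symptom severity group have been met". It does not say which group numbers are meant, what happens to a group once it is full, or how the rule relates to 1320.

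**The concern.** A total and three group minimums are different criteria, because the number of patients falling in each group is random. If every group must reach its number and none is closed, recruitment runs until the slowest group fills while the others overshoot. The final sample size, the screening load and the timeline then depend on choices that the text does not make.

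The group numbers now decide when the trial stops, so it also matters whether they are the sizes the stated power requires. If the scarce groups' numbers are larger than needed, they prolong recruitment for no purpose the plan states.

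**Working it through.** **Inputs (Sample size section).** Group numbers 740/158/158; shares 70/15/15%; effects 0.2 SD (minimal/mild) and 0.5 SD (moderate, severe) at 80% power; overall 0.2 SD at 90% power; two-sided 5%; attrition 20%; 22,000 invitations for 1320.

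**Reproducing the plan's total.**
- 740 + 158 + 158 = 1056, and 1056 / 0.8 = 1320, as stated.
- Overall comparison: n per arm = 2(1.960 + 1.282)² / 0.2² = 526, against 528 stated. This agrees.

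**Group sizes from their own inputs.**
- 0.2 SD, 80%: 2(1.960 + 0.842)² / 0.2² = 393 per arm, against 370 stated. Power at 370 per arm is about 77.5%.
- 0.5 SD, 80%: the same formula with 0.5² gives 63 per arm, or 64 with the t distribution (80.1% power), so 128 in all. At 78 per arm power is about 87%.
- The printed numbers are instead the shares of the total: 0.70 × 1056 = 739.2 and 0.15 × 1056 = 158.4. Also, 78 per arm makes 156, not 158.

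**Group numbers inflated for attrition.** 740 / 0.8 = 925 and 158 / 0.8 = 197.5, so 198 each; the sum is 1321. The article does not print these; they are one reading of the rule.

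**When the rule stops.** Arrivals were simulated one at a time with the given shares, counting until all three numbers are reached (10,000 runs at 70/15/15, no group closed):

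| Numbers to be met | Mean stop | Median | 5th–95th percentile | Stopped by 1320 |
|---|---|---|---|---|
| 925/198/198 | about 1390 | 1372 | about 1330–1500 | essentially never |
| 740/158/158 | about 1116 | 1101 | about 1064–1211 | about 99.9% |

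**Consequences at 70/15/15.**
- Inflated numbers: 1390 / 1320 = 1.05, an overrun of about 5%. The planned yield is 1320 / 22,000 = 6%, so 1390 / 0.06 ≈ 23,200 invitations.
- Printed numbers: the attrition allowance is 1320 − 1056 = 264, and only 1116 − 1056 = 60 of it is recruited. After 20% loss the overall test has 1116 × 0.8 / 2 ≈ 446 per arm and about 85% power, against 90% stated. If minimal/mild stands at its bare 740, 740 × 0.8 / 2 = 296 per arm gives about 68%.

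**Other splits (assumptions; the protocol gives none).** With inflated numbers and open groups: 72/14/14 gives about 1470, 75/12.5/12.5 about 1645, 80/10/10 about 2060.

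**The proposed floor.** 64 / 0.8 = 80 per arm, so 160 recruited per scarce group. At 1320 and a 15% share the expected count is 198 with SD √(1320 × 0.15 × 0.85) ≈ 13, so 160 lies about three SDs below. Both floors are met about 99.8% of the time.

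**The case against.** The best defence is that only one stopping rule is written. On this view 1320 is a planning total built from the group needs, nothing calls it a cap, and the two agree in expectation, since the inflated group numbers sum to 1321. This stands. A reader might infer a flat contradiction, or that the rule overruns 1320 even if the observed split is exactly 70/15/15. The document supports neither: an exactly realised split gives 924/198/198 at 1320, and the rule ends within two patients of it. The overrun comes from chance variation around true shares of 70/15/15.

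It is also fair that the overrun needs the inflated numbers and open groups. Closing full groups would give about 1320 randomised whatever the split. But Eligibility criteria do not mention severity group, and under Allocation randomisation follows the prediction tool automatically, so open groups are the natural reading. Closure would also let quotas set the case mix of the overall comparison. With the plan's hypothesised effects and an assumed natural mix of 80/10/10, the overall effect would be 0.7 × 0.2 + 0.3 × 0.5 = 0.29 SD instead of 0.8 × 0.2 + 0.2 × 0.5 = 0.26 SD. That difference is 0.03 × 6.75 ≈ 0.2 PHQ-9 points, and it rests on two assumptions.

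The rule does not threaten type I error. Group membership is fixed at baseline, no interim analysis is planned, and randomisation and the models account for severity group. Finally, sizing on subgroups was a deliberate choice, and a plain cap at 1320 would abandon it. That stands too, and is why the fix keeps a floor.

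**Conclusion.** The point holds as an unreconciled rule with misdescribed group sizes. At the protocol's own 70/15/15 shares with open groups, the expected total is about 1390 or about 1116, depending on which group numbers are meant; neither is 1320. The first is a modest overrun of about 5%. The second costs more, because it gives up about three quarters of the attrition allowance (204 of 264).

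A reader might take from this that the trial needs about 2000 participants. The document does not support that as a forecast: it requires a group share near 10%, and the protocol gives no split but 70/15/15.

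The error in the group sizes does not depend on how the rule is read. The 158 is above the 80%-power size for 0.5 SD, and the 740 is below that for 0.2 SD. The overall 90% power at 1056 evaluable is correct. All powers here are for a simple two-sample comparison; the planned baseline adjustment could raise them. The 20% loss is the protocol's 12-month figure, so loss at the three-month primary endpoint may be smaller.

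**What to change.** In Sample size, correct the group figures: 128 evaluable (64 per arm) are enough for 0.5 SD at 80% power; 78 per arm gives about 87%; 370 per arm gives about 77.5% for 0.2 SD. Resolve 158 against 78 per arm.

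In Recruitment, replace the closing sentence with a rule that recruitment stops at 1320 randomised, no group is closed, and enrolment goes on past 1320 only if the moderate or severe group has fewer than 160 recruited. Report subgroup power at the sizes achieved.

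The cost is a few sentences. Power in the scarce groups may end nearer the stated 80% than the 87% the present numbers give, and the minimal/mild group has no separate guarantee. The floor can still prolong recruitment if a scarce group's share falls below about 160 / 1320 = 12%; at an assumed 10% it would need about 160 / 0.10 = 1600, against 198 / 0.10 = 1980 under the inflated numbers.
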